# Behavioral economics-based incentives supported by mobile technology on HIV knowledge and testing frequency among Latino/a men who have sex with men and transgender women: Protocol for a randomized pilot study to test intervention feasibility and acceptability

**DOI:** 10.1186/s13063-018-2867-1

**Published:** 2018-10-05

**Keywords:** Feasibility and acceptability, HIV testing, Mobile technology, Behavioral economics, Intervention, Incentives, Latino, Men who have sex with men, Transgender women

## Abstract

**Background:**

Mobile Technology and Incentives (MOTIVES) is a randomized pilot study of a mobile technology-based and behavioral economics-supported HIV prevention intervention. Behavioral economics (BE) uses financial incentives in a way that departs from the traditional focus on large monetary payments. Instead, BE suggests that relatively small “nudges” can effectively initiate and sustain behavior change. This pilot study examines the feasibility and acceptability of an HIV prevention intervention that uses text messages in combination with BE incentives to improve retention of HIV prevention information and increase frequency of HIV testing among Latino/a men who have sex with men (MSM) and transgender women (TGW). The pilot will also estimate mission-critical design parameters with point and confidence interval estimates of the intervention to inform a future, fully powered effectiveness study.

**Methods:**

The project will be conducted in collaboration with Bienestar Human Services, Inc. (*Bienestar*), a non-profit community-based service organization. The intervention is being tested in a small, randomized controlled trial to pilot the intervention’s feasibility and acceptability among 200 Latino/a MSM and TGW from *Bienestar*’s HIV testing sites. Information on feasibility will include recruitment, refusal, and retention rates as well as message sending success rates; acceptability will include perceived appropriateness based on responses to the intervention. Participants will be randomized into either the “information only” control group (e.g. receiving text messages with HIV prevention information) or the “information plus” intervention group (e.g. additionally receiving quiz questions that provide the possibility of winning prizes). Participants will be followed for 12 months from enrollment. In addition to using data abstracted from *Bienestar*’s routine data collection mechanisms, we will also collect survey data (blinded outcome assessment) from participants at 0, 6, and 12 months to provide an initial assessment of whether incentives affect their level of HIV knowledge and testing frequency.

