At enrollment, we will take several steps to ensure the confidentiality of participants related to text message communication. For example, as mentioned above, MOTIVES HIV testers will instruct participants how to properly use the SMS system, maintain privacy on their device, and delete SMS messages from their mobile device. Finally, study staff will call the participant (either using an office line or using the *67 feature to make a protected call using their personal cell phone) to confirm that study staff has the correct cell phone contact number for the participant. At this time, participants will receive a $15 gift card.

After participating in the baseline survey and receiving their gift card, participants will be randomized using computer allocation by the study PI. The goal is to ensure that the randomization process does not influence responses to the baseline survey (e.g. responding more quickly if they were not chosen for the prize drawing group and feeling disappointed and less invested in the study). The study design was guided by its purpose as a pilot trial; we used a 1:1 randomization as it provides the greatest power for testing effectiveness in preparation for a future definitive RCT. Hereafter we will refer to the two groups as: (1) Information plus group (intervention group); and (2) Information only group (control group). HIV testers will also reaffirm that assignment is completely random and not based on the personal characteristics of any individual client. RAND study staff will explain to testers why randomization is so important, underscoring that only with their help can we actually understand if the intervention works. If testers select participants based on their own judgment of who is most in need of the intervention (e.g. they think a client appears particularly poor and would really appreciate having gift cards), we would not be able to collect accurate data. If a certain type of client is consistently included in the information plus reminders group, we will not be able to determine if the intervention works with everyone or just with a particular type of person.

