### Measures: health outcomes

Enrolled participants respond to a baseline assessment after they have completed screening and consent. The MOTIVES HIV tester reads the baseline survey to participants to guarantee understanding by clients across a range of literacy levels. Together the screening and consent processes take approximately 15 min to complete; the baseline survey takes approximately 30 min. Participants will complete a shortened six-month survey via response to a link sent to them on their phone. If participants cannot complete the six-month survey on their own, the Study Coordinator will offer to meet them at a local library of their choice and provide a tablet to complete the survey. However, we expect this circumstance be the exception rather than the rule. Participants will receive a $15 gift certificate via text after completing the six-month survey.

The 12-month follow-up survey will have fewer questions and will be completed after the intervention is over, Thus, completing the questions at a *Bienestar* testing location will not confound the outcome of interest. Participants will receive a $15 gift card for participating in the final survey. For those who do not complete their HIV test for that period, we will send a text message reminder to complete the final survey at *Bienestar*. Table 1 describes when each set of questions will be asked.

**Table 1 Tab1:** Health outcomes and measures of interest

Outcome	Instrument	Data collection timepoint
Primary Outcome		
HIV knowledge	Carey MP, et al. Development and psychometric evaluation of the brief HIV knowledge questionnaire (hiv-kq-18). AIDS Education and Prevention. 2002; 14: 174-184.	enrollment, 6 & 12 months
HIV testing behaviors	Extracted from *Bienestar* clinic data	
Secondary Outcomes		
HIV infection	Oraquick/Orasure	enrollment, 3, 6, 9 and 12 months
Covariates of Interest		
Socio-demographic information	Based on previous *Bienestar* questionnaire	enrollment & 12 months
Acculturation	Marín, G et al. Development of a short acculturation scale for Hispanics. Hispanic Journal of Behavioral Sciences. 1987; 9:183–205.	
Mental health	Kessler, RC et al. Short screening scales to monitor population prevalences and trends in non-specific psychological distress. Psychological Medicine. 2002; 32: 959-956.	
Substance abuse	Carballo-Diéguez, A et al. Microbicide Safety and Acceptability in Young Men: Baseline Behavioral Questionnaire. 2010.	

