### Data analysis

As previously stated, the primary goal of the analysis is to estimate the intervention’s acceptance and feasibility by determining enrollment and retention rates in the study, using the number of clients screening positive for eligibility, the number of clients enrolling in the study per month, percentage of enrolled clients who respond to the weekly quizzes and are eligible to participate in the testing-based prize drawings, and participants retained in the study. To assess participants’ acceptance of the intervention, we will also ask them to rate their program experience. Semi-structured exit interviews after the study is completed will also provide valuable feedback about the acceptability of the program to clients and the feasibility of the intervention procedures as viewed by clinic personnel.

We will conduct interim data checks to ensure that certain individuals (e.g. either high or low income) are not systematically declining participation in the study. Data checks will be supplemented with bi-weekly team calls in which we review recruitment and retention goals, address issues that arise in the field, and refine our strategy for moving forward. Because most of the study data are uploaded electronically, we avoid issues of double data entry. Interim data checks help ensure the accuracy of data provided.

Blinding participants and staff to the study design raises several issues. Participants will know if they are in the intervention (Information plus group) versus control (Information only group) as the former will be receiving weekly quiz options. However, with the exception of the site PI and the research analyst at RAND responsible for sending all text messages, study staff will be blinded to the data identifiers. All data for subsequent analysis will be de-identified and only the PI and Co-Investigators will have access to the study data. Data will only be unblinded in the case of an AE or SAE, for which the RAND PI needs immediate access to all information to ensure participant safety.

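### The abstract labels the survey a blinded outcome assessment, but the 6- and 12-month answers come from participants who know their arm, and masking of staff or analysts to arm is not established

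*Protocol article*

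**What the plan says.** The abstract (Methods) attaches the phrase "survey data (blinded outcome assessment" to the survey at 0, 6 and 12 months. It gives the survey's purpose as a first look at whether incentives affect HIV knowledge and testing frequency.

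The Data analysis section then describes who knows what:

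- On participants: "Participants will know if they are in the intervention (Information plus group) versus control (Information only group".
- On staff: "study staff will be blinded to the data identifiers", and this applies "with the exception of the site PI and the research analyst at RAND responsible for sending all text messages".
- On access: the data are de-identified, and "only the PI and Co-Investigators will have access to the study data".
- On breaking the blind: "Data will only be unblinded in the case of an AE or SAE", the reason given being that the RAND PI then needs full information at once.

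The MOTIVES intervention section says that, after the baseline survey, "participants will be randomized using computer allocation by the study PI".

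Measures: health outcomes gives the mode of each survey. At baseline, "The MOTIVES HIV tester reads the baseline survey to participants". At six months the participant answers through a link on the phone, with a coordinator and tablet as an exceptional fallback. At 12 months the survey is completed at a Bienestar location, and no administrator is named. Table 1 takes HIV knowledge from a fixed questionnaire (HIV-KQ-18), testing behaviour from clinic data and HIV infection from a rapid test.

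**The concern.** Blinded outcome assessment means that whoever produces or judges the outcome does not know the arm. In a self-completed questionnaire that person is the respondent, and the protocol says that respondents know their arm. Removing identifiers from a dataset protects confidentiality, but a de-identified record can still carry the arm.

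The protocol itself recognises that knowledge of allocation can change survey answers. The MOTIVES intervention section places randomisation after the baseline survey so that participants disappointed at missing the prize group do not hurry through it or lose interest. The same reasoning applies at 6 and 12 months, when every participant knows the arm.

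HIV knowledge is a primary health outcome, and the Data analysis section also plans to compare self-reported sexual behaviours between arms. The pilot is meant to supply planning parameters for a definitive trial, including response profiles for retention of prevention information. A planner who relies on the abstract's label would credit those estimates with a protection that the body of the article does not provide.

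**Working it through.** No formula or stated figure bears on this point. The check sets the statements side by side.

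**Step 1. The label, wave by wave** (MOTIVES intervention; Measures: health outcomes; Data analysis)

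| Wave | Relative to randomisation | How answered | Respondent knows arm? | Survey staff masked to arm? |
|---|---|---|---|---|
| Baseline | Before | Read aloud by the tester | No, not yet assigned | Not applicable, not yet assigned |
| 6 months | After | Self-completed by phone link | Yes | Not stated; normally no interviewer |
| 12 months | After | At a Bienestar location, administrator not stated | Yes | Not stated |

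The respondent is aware of the arm in 2 of 3 waves, and these are the only 2 that can show an effect of the intervention.

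**Step 2. Outcome by outcome** (Table 1; Data analysis)

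- HIV knowledge: answered by the participant, so exposed at 6 and 12 months.
- Self-reported sexual behaviours: exposed in the same way.
- HIV testing: extracted from clinic records. Knowing the arm may change whether people test, which is the intended effect, but respondent awareness does not affect how a test is recorded.
- HIV infection: rapid test, so respondent awareness does not affect the measurement.
- Recruitment, refusal and retention rates: not covered by the label and unaffected.

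**Step 3. Can staff or analyst masking rescue the label?** The staff sentence names data identifiers, and its scope can be read in two ways.

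- If identifiers means personal identifiers, the sentence describes de-identification and says nothing about arm.
- If it was meant to include the arm code, some staff are masked, but the article does not say whether these are the people who administer, score or analyse the survey. The respondent is still unblinded.

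Neither reading makes the 6- and 12-month answers a blinded assessment.

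**Step 4. The unblinding sentence against the roles.** Allocation is by the study PI. Access to data is given to the PI and Co-Investigators. The exemption from masking names the site PI. The AE/SAE sentence names the RAND PI. The article does not say which of these titles refer to the same person.

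- If the study PI is the RAND PI, the person who would need the data unblinded has carried out the allocation.
- If they are different people, the text does not say which of them is masked to what.
- If unblinding means re-linking records to named persons, the sentence can coexist with allocation by a PI, but it then gives no support to a claim of masking to arm.

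Under each reading the text needs reconciling.

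**The case against.** The strongest reply is that little is at stake. The Data analysis section openly says that participants are unblinded, so a reader of the whole article is not misled. HIV-KQ-18 is a fixed questionnaire with little room for scorer judgement. The other primary outcome comes from clinic records, and the stated primary goal is feasibility and acceptability. The AE/SAE sentence and the named exemptions show that some masking was intended. All of this stands and limits the size of the point. It does not remove the conflict between the abstract and the body, because the exposure lies with the respondent and not the scorer.

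A reader might be tempted further than the documents allow:

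- **That no protection exists at all.** The text leaves the scope of masking unclear. It does not show that scorers or analysts know the arm.
- **That only the intervention arm has practised looking up answers.** The weekly information texts carry a link and go to both arms. The quiz feedback adds a further link for one arm, but nothing describes rehearsal, and the quiz is part of the intervention.
- **That the plan says the PI is unblinded only for an AE or SAE.** The sentence concerns the data.
- **That the study, site and RAND PI are one person.** The article does not say so.
- **That someone other than the PI should hold the allocation list.** That is a preference. Recruitment was stated to run to 9 May 2018 and the article appeared on 5 October 2018, so on those dates allocation was already complete.

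Masked arm codes at analysis are commonly left to an analysis plan. Their absence from the article is not the error; they are offered below as part of the remedy.

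**Conclusion.** The point holds in a limited form. The label is contradicted for the 6- and 12-month survey answers, and masking of survey staff, scorers and analysts to arm is not established by anything in the article. It affects one of two primary health outcomes and the self-reported behaviours, in both post-randomisation waves. The direction and size of any resulting bias cannot be derived from the document.

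This rests on two readings: that the abstract's parenthesis covers all three waves, as its sentence structure indicates, and that data identifiers carries its ordinary meaning. The second could be relaxed without changing the conclusion about respondents. The correction should be made because it changes how the survey results may be interpreted. It does not call the feasibility and acceptability aims into question.

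**What to change.** 1. Delete the blinded-assessment label for the 6- and 12-month surveys. State that HIV knowledge and self-reported behaviours come from respondents who know their arm, and that testing from clinic records is the objective outcome.
2. State who is masked to arm among 12-month survey staff, scorers and analysts, separately from who is denied personal identifiers.
3. Define study PI, site PI and RAND PI, and reconcile those roles with the sentence on unblinding. Say whether unblinding there means revealing the arm or re-linking records to persons.
4. Run the between-arm analysis on masked codes (A/B) until the analysis code is final. On the stated dates this was still possible at publication: the last enrolment on 9 May 2018 plus 12 months of follow-up runs to about 9 May 2019.

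The cost is a few sentences, one recoded variable and some data handling, with no change to conduct or sample size. The drawback is a less favourable description of the survey outcomes.

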**Discussion:**

If shown to be acceptable, feasible, and resource-efficient, MOTIVES will provide an innovative way to communicate the latest HIV prevention information and support trimestral HIV screening among Latino/a MSM and TGW.

**Trial registration:**

ClinicalTrials.gov, NCT03144336. Registered on 5 May 2017.

## Background

In the United States, men who have sex with men (MSM) and transgender women (TGW) continue to be disproportionally affected by HIV, with racial and ethnic minority MSM and TGW carrying the largest HIV burden. There are few evidence-based effective HIV prevention interventions available for racial and ethnic minority MSM and TGW; biomedical breakthroughs that could offer additional prevention strategies need to be effectively communicated to these populations. Given the quickly changing nature of prevention information and guidelines, a communication framework is required that can be adapted as new information emerges.

Racial and ethnic minority MSM and TGW face unique challenges in accessing and understanding the most up-to-date prevention information. Mobile technologies offer a low-cost yet effective way to remain in contact with these populations; studies suggest that the technologies might be a critical mechanism for relaying HIV-related information [1–5]. Over half (64%) of Americans own a smartphone; Latinos and blacks are three to four times more likely than whites to depend on their smartphone as a primary tool for communication and online access [6]. However, despite the promise of these technologies for enhancing communication with these populations [7–12], studies have noted that participants face multiple challenges when trying to engage with the technologies [13] or abandon them after a short time [14–16].

We are piloting a small randomized controlled trial (RCT) to examine the feasibility and acceptability of integrating mobile technologies and behavioral economics (BE) in a novel way to reach Latino/a MSM and TGW with information about HIV prevention. In the formative phase of this study, focus groups with study participants generated some key lessons for how to use mobile technology with our populations of interest, including: consider requiring ownership of a smartphone (rather than a basic cell phone) to enroll in the study; send messages at the same time and day of the week; allow for personalization of messages; give concrete examples of potential texts so participants know what to expect; and work with a trusted community partner to tailor message structure and content. We also learned that small financial incentives could support participant retention, increase engagement with prevention information and HIV-testing frequency, and support individuals in their goal to remain HIV-negative. We are applying these lessons in designing the current intervention, which we describe here.

BE suggests that small, frequent “nudges” can effectively alter behavior. The “nudge” in our RCT takes the form of a chance to win a prize. Rather than focus on the magnitude of the prize, BE suggests that the way prizes are given out – and at what time intervals – determines their effectiveness. Prize drawings leverage the bias of overestimating small probabilities (leading individuals to participate in the drawing because they overestimate their chance of winning) and also increase salience (frequent prizes keep a behavior high on a person’s mental priority list). Rewards given out through prize drawings also exploit the motivational power and pleasure of games of chance. A number of studies have documented the effectiveness of lotteries in affecting complex health behaviors such as breastfeeding, weight reduction, as well as obesity and cardiovascular disease prevention [17], in addition to targeting sexual behavior [18].

There are few published studies of using prizes for HIV-related behaviors; however, preliminary results from an ongoing study by the principal investigator (PI) [R34MH096609] to improve adherence using small lottery prizes in Uganda show promise. Over the first nine months of that study, individuals receiving incentives were nearly 25% more likely to achieve 90% antiretroviral adherence compared with the control group [19]. Taken together, these studies suggest further exploration of how lotteries support individuals in their effort to maintain their HIV-negative status.

In this pilot RCT, we focus on the local population of Los Angeles County, where Latino/a MSM and TGW are disproportionately impacted by HIV. The estimated HIV prevalence is 40% among Latino MSM [20] and 17% among Latina TGW [21]. MOTIVES—the **Mo**bile **T**echnology and **I**ncenti**ves** intervention—pilots a novel way to reach and support Latino/a MSM and TGW, who are hard to contact and have difficulty accessing relevant information about HIV prevention. We are pairing mobile technologies, a low-cost way to relay the most up-to-date prevention information, with incentives to encourage ongoing participation and translate key prevention messages into healthy behaviors. Our goal is to assess the feasibility and acceptability of the proposed intervention and associated outcome measures among potential participants and program staff to inform a definitive RCT on intervention effectiveness in the future.

## Methods/Design

This pilot study satisfies all checklist items in the CONSORT extension for randomized pilot and feasibility trials by Eldridge and colleagues [22].

